## 2. LAY SUMMARY

The build-up of fat in the liver can cause inflammation and a lot of scarring in the liver. This condition is called compensated cirrhosis due to non-alcoholic fatty liver disease (CC-NAFLD). It is a serious disease that may require liver transplant and increases the risk of early death. It affects about 200,000 UK adults, most of whom are also living with obesity.

Currently, there is no drug available to treat CC-NAFLD. Weight loss programmes might improve it, but only if they lead to large weight loss. One programme that could achieve this on a large scale is a low-energy diet with professional support. In this programme, people eat only soups and shakes for 16 weeks (about 860 calories per day). Then, slowly over the next 8 weeks, they swap some soups and shakes for regular food. The support helps people stick to the programme and develop healthier eating habits. We know people lose weight rapidly and lower their risk of heart disease. This may also be a good treatment for CC-NAFLD, but there is a concern that rapid weight loss may worsen scarring in the liver. Here we will test the programme in a small group of people with detailed monitoring of the health of their liver to see if this concern is a reality.

We will recruit 24 adults with CC-NAFLD and excess weight. A computer will decide at random if patients continue with their care as usual (n=8) or are offered the programme (n=16). We will see whether enough patients are willing to take part in the trial, stick to the programme, and return for follow up visits. We will examine whether the treatment appears to be safe at 2, 4, 16, and 24 weeks with blood tests. If there are signs of worsening of the disease, we will stop the treatment. At the start of the programme and at 24 weeks, we will do a liver scan to make a more detailed assessment of liver scarring. We will also monitor changes in weight, body composition, risk of heart disease, and physical function.

This information will tell us if we can confidently plan a full trial to test whether this programme can delay progression of this liver disease.

We will publish the results in a scientific journal and present them to doctors treating liver disease.

## 3. SYNOPSIS

|                                 |                                                                                                                                                                                                                                                           |
|---------------------------------|-----------------------------------------------------------------------------------------------------------------------------------------------------------------------------------------------------------------------------------------------------------|
| Study Title                     | Safety signals and potential efficacy of a low-energy total diet replacement programme with behavioural support to delay disease progression in compensated cirrhosis due to non-alcoholic fatty liver disease: a feasibility randomised controlled trial |
| Internal ref. no. / short title | LiFT 2: Low-energy treatment in compensated cirrhosis                                                                                                                                                                                                     |
| Study registration              | ISRCTN: https://www.isrctn.com/ISRCTN13053035                                                                                                                                                         |
| Sponsor                         | University of Oxford, RGEA
[name]                                                                                                                                                          |
| Funder                          | National Institute for Health Research Oxford Biomedical Research Centre (NIHR Oxford BRC)
E: [contact]                                                                                     |
| Study Design                    | Randomised controlled trial                                                                                                                                                                                                                               |

|                            |                                                                                                                                                 |                                                                                        |                   |
|----------------------------|-------------------------------------------------------------------------------------------------------------------------------------------------|----------------------------------------------------------------------------------------|-------------------|
| Study Participants         | People with compensated cirrhosis due to non-alcoholic fatty liver disease and body mass index $\geq 30 \text{ kg/m}^2$                         |                                                                                        |                   |
| Sample Size                | 24                                                                                                                                              |                                                                                        |                   |
| Planned Study Period       | Total trial length: 3 years
Individual participant's involvement: approx. 6 months
Long-term follow-up via medical records: up to 2 years |                                                                                        |                   |
| Planned Recruitment period | February 2022 – September 2022                                                                                                                  |                                                                                        |                   |
|                            | Objectives                                                                                                                                      | Outcome Measures                                                                       | Timepoint(s)      |
| Primary                    | i. To assess the safety signals of the intervention                                                                                             | i. Criteria of severe changes in biochemistry (ALT, AST, total bilirubin)              | 0, 2, 4, 16, & 24 |
|                            | ii. To assess the potential efficacy of the intervention in improving a marker of liver inflammation/fibrosis                                   | ii. Iron-corrected T1 relaxation time (cT1) values by magnetic resonance imaging (MRI) | 0 & 24            |
|                            | iii. To assess the potential efficacy of the intervention in not worsening MRE-estimated liver stiffness, a marker of liver fibrosis            | iii. Liver stiffness by magnetic resonance elastography (MRE)                          | 0 & 24            |
| Secondary                  | To examine changes in liver stiffness by transient elastography                                                                                 | Liver stiffness by transient elastography                                              | 0, 16, & 24       |
|                            | To examine changes in liver fat                                                                                                                 | i. Proton density fat fraction (PDFF)                                                  | 0 & 24            |
|                            |                                                                                                                                                 | ii. Controlled attenuation parameter                                                   | 0, 16, & 24       |
|                            | To examine changes in blood biomarkers                                                                                                          | i. ELF                                                                                 | 0 & 24            |
|                            |                                                                                                                                                 | ii. UKELD score                                                                        | 0, 4, 16, & 24    |
|                            |                                                                                                                                                 | iii. CP score                                                                          | 0, 4, 16, & 24    |
|                            | To examine changes in physical performance                                                                                                      | i. Physical performance test
ii. Liver frailty index                                | 0 & 24
0 & 24  |
|                            | To examine adverse events                                                                                                                       | Adverse events                                                                         | 0, 2, 4, 16, & 24 |
|                            | To examine changes in weight                                                                                                                    | Body weight                                                                            | 0, 4, 16, & 24    |

|                         |                                                                                                                                                                                                                                    |                                                                                                                                                                                                                                                                                                                                                                                                             |                                                                                                                    |
|-------------------------|------------------------------------------------------------------------------------------------------------------------------------------------------------------------------------------------------------------------------------|-------------------------------------------------------------------------------------------------------------------------------------------------------------------------------------------------------------------------------------------------------------------------------------------------------------------------------------------------------------------------------------------------------------|--------------------------------------------------------------------------------------------------------------------|
|                         | 
To examine changes in total fat-free mass
 
To examine changes in visceral fat
 
To examine changes in muscle mass
                                                                                                | 
Total fat-free mass on bioelectrical impedance
 
Visceral fat on MRI
 
Muscle mass on MRI
                                                                                                                                                                                                                                                                                                  | 
0, 4, 16, & 24
 
0 & 24
 
0 & 24
                                                      |
| Exploratory      | 
To examine changes in medication
 
To examine changes in cardiometabolic markers
                                                                                                                                       | 
Adjustment in the number and dose of medication
 
i. Blood pressure
ii. HbA1c
iii. Lipid profile
                                                                                                                                                                                                                                                                                        | 
0, 4, 16, & 24
 
0, 4, 16, & 24
0, 16, & 24
0 & 24
                             |
| Process measures | 
To examine feasibility of recruitment
 
To examine intervention engagement
 
To examine retention rate
 
To examine satisfaction with the intervention
 
To monitor alcohol intake throughout the study
 | 
i. Number of potentially eligible participants
ii. Proportion of eligible participants randomised
iii. Reasons for non-enrolment
 
i. Proportion of sessions attended
ii. Reasons for non-engagement
 
i. Proportion of randomised participants completing a 24-week follow-up visit
ii. Reasons for dropout
 
Feedback questionnaire
 
Alcohol intake questions
 | 
0
 
0
 
0
 
0, 4, 16, & 24
 
2, 4, 16, & 24
 
24
 
0, 4, 16, & 24
 |
| Intervention(s)  | Low-energy total diet replacement programme with behavioural support.                                                                                                                                                              |                                                                                                                                                                                                                                                                                                                                                                                                             |                                                                                                                    |
| Comparator       | Care as usual                                                                                                                                                                                                                      |                                                                                                                                                                                                                                                                                                                                                                                                             |                                                                                                                    |

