#### Feedback questionnaire (5 min)

Participants will be given a study-specific version of a feedback questionnaire (adapted from a previous study) on various aspects of the trial and of the intervention (for participants in the intervention group) to complete at home and return in a pre-paid envelope by post.

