#### Follow-up visit 4 at 24 weeks ( $\pm$ 3 weeks) (~3h)

The fourth follow-up study visit will include the same assessments as the follow-up visit 2 plus the feedback questionnaire.

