## **9.10. Early Discontinuation/Withdrawal of Participants**

During the course of the study a participant may choose to withdraw early from the study treatment at any time. This may happen for several reasons, including but not limited to:

- The occurrence of what the participant perceives as an intolerable AE.
- Inability to comply with study procedures
- Participant decision

Participants in the care as usual group: They may opt out of study assessments but may remain on study follow-up.

Participants in the intervention group: They may stop the intervention and/or study assessments but may remain on study follow-up and will be encouraged to do so. However, if they choose not to attend the 2-week or 4-week safety assessment, they will not be able to continue the intervention but can remain on study follow-up. The visits should be completed within the specified window (as per section 9.8) but provisions will be made on a case-by-case basis to have this assessment completed outside this window in exceptional circumstances (e.g. if the patient is self-isolating due to COVID-19 but is keen to get assessed and resume the intervention).

All participants may also withdraw their consent, meaning that they wish to withdraw from the study completely. In the case of withdrawal from both treatment (intervention) and active follow up, the following options for a tiered withdrawal from the study will be given to participants and explained in the participant information sheet. According to the design of the trial, participants may have the following three options for withdrawal;

- 1) Participants may withdraw from active follow-up and further communication but allow the trial team to continue to access their medical records and any relevant hospital data that is recorded as part of routine standard of care; i.e., imaging scans, blood results, and disease progression data, etc.
- 2) Participants can withdraw from the study but permit data and samples obtained up until the point of withdrawal to be retained for use in the study analysis. No further data or samples would be collected after withdrawal.

In addition, the Investigator may discontinue a participant from the intervention at any time if the Investigator considers it necessary for any reason including, but not limited to:

- Pregnancy
- Ineligibility (either arising during the trial or retrospectively having been overlooked at screening)
- Significant protocol deviation

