- Significant non-adherence with treatment regimen or trial requirements
- An adverse event which requires discontinuation of the trial intervention or results in inability to continue to comply with trial procedures
- Disease progression which requires discontinuation of the trial intervention or results in inability to continue to comply with trial procedures
- Criteria of the algorithm in Appendix E are met.
- If enhanced observation is necessary as per section 10 but is not possible

The follow-up of participants that have withdrawn from the intervention but not from active follow-up will continue with the standard follow-up assessments of the study.

If the intervention is discontinued due to criteria in Appendix E, the intervention may be re-introduced with approval of the Trial Steering, Data Monitoring, and Ethics Committee (TSDMEC) if another cause of the elevation is identified. If on re-introduction, the elevations in liver function tests persist, the intervention must be discontinued and enhanced observation must continue as per section 10. Data from randomised participants will be analysed and post-randomisation withdrawal from the study will not result in exclusion of the data for that participant from the analysis. If the participant is withdrawn before randomisation, they will be replaced (as per section 9.3). The type of withdrawal and reason for withdrawal will be recorded in the CRF. If the participant is withdrawn due to an AE, the Investigator will arrange for frequent telephone calls as agreed with the participant (or an ad-hoc study visit upon the study clinician's judgement) until the AE has resolved or stabilised (also see sections 9.7, 10, and 13.3.2). If a participant is withdrawn from treatment due to pregnancy the pregnancy will be followed-up to outcome. See the Safety Reporting section below.

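### The only satisfaction measure is scheduled solely with the week-24 visit, with no route for participants who leave follow-up or miss that visit

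*Protocol*

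**What the plan says.** The Synopsis (section 3) and section 6 list, among the process measures, the objective "To examine satisfaction with the intervention". It has one outcome measure, the feedback questionnaire, and one time point, week 24.

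Section 9.8 says that follow-up visit 4 "will include the same assessments as the follow-up visit 2 plus the feedback questionnaire". In Appendix B the questionnaire row is marked in the week-24 column and nowhere else, including the ad-hoc visit column.

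Section 9.6.3 describes a study-specific form about the trial and, for the intervention group, about the programme. Participants receive it "to complete at home and return in a pre-paid envelope by post".

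Section 9.10 separates stopping the diet from leaving the study. Of intervention participants it says: "They may stop the intervention and/or study assessments but may remain on study follow-up and will be encouraged to do so". Those "withdrawn from the intervention but not from active follow-up will continue with the standard follow-up assessments of the study". One of the withdrawal options listed there reads: "Participants may withdraw from active follow-up and further communication but allow the trial team to continue to access their medical records". The other listed option ends all further data collection.

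Information on people who leave is also gathered in other ways. The retention objective includes "ii. Reasons for dropout", the engagement objective includes reasons for not engaging, and the type of and reason for withdrawal go into the CRF (section 9.10).

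**The concern.** A form scheduled only with the last visit is, by plan, offered to people who reach that visit. Those who found the diet or the trial hard to accept are plausibly over-represented among those who do not, so the likely direction of any selection is towards a favourable picture.

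This is a matter of data collection rather than analysis. A statistical analysis plan can describe the respondents, but it cannot recover ratings that nobody asked for.

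At stake is what the team learns about acceptability before planning a full trial. If retention falls in the Amber band of section 11.10, the decision is to go ahead with modifications. Ratings from leavers, on the same items as those from stayers, would help to show what to modify.

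**Working it through.** No figure for satisfaction is stated in the protocol, so the check is who is due the form and how many could be missed.

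**Who is due the form, from sections 9.8, 9.10 and Appendix B**

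| Participant | Form scheduled? |
|---|---|
| Completes the diet and attends week 24 | Yes |
| Stops the diet, stays in active follow-up, attends week 24 | Yes (standard assessments continue) |
| Stops study assessments but remains on study follow-up | No route described |
| Misses week 24 without withdrawing | No route described |
| Withdraws from active follow-up and further communication, or from all data collection | No, and cannot be approached after withdrawal |

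The third and fourth rows are the avoidable part, together with anyone in the fifth row who would have accepted a form at the moment of leaving.

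**The plan's own dropout figure (section 11.3)**

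- Inputs: 22 evaluable (15 intervention, 7 control), 24 randomised (16 and 8), dropout approximately 10%.
- Implied dropout: 1 − 22/24 = 8.3%. At exactly 10%, 22/0.90 = 24.4. The stated 24 agrees with an approximate 10%.
- By arm, the plan allows for 16 − 15 = 1 intervention and 8 − 7 = 1 control participant lost.

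**Expected number without a form**, taking dropout to mean missing the week-24 visit:

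- At 10%: 0.10 × 16 = 1.6 intervention participants and 0.10 × 24 = 2.4 overall. This is about 1 to 2 of 16 and about 2 of 24.
- At Amber retention (66% to 84%, section 11.10), assuming the overall rate applies equally to the intervention arm: 0.84 × 16 = 13.4 and 0.66 × 16 = 10.6. The whole numbers inside the band run from 13/16 = 81% to 11/16 = 69%, so 3 to 5 of 16 would have no form.

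**What that could do to a reported proportion**

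The protocol defines no percent-satisfied summary, so this is an illustration. For any yes/no item, if k of 16 forms are missing, the proportion among all 16 can lie anywhere in an interval of width k/16:

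- k = 1: 1/16 = 6 percentage points
- k = 2: 2/16 = 12.5 points
- k = 3: 3/16 = 19 points
- k = 5: 5/16 = 31 points

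For example, assume 80% of respondents are favourable (an assumed value) and k = 2. The favourable count among respondents is 0.80 × 14 = 11.2. The proportion among all 16 then lies between 11.2/16 = 70% and (11.2 + 2)/16 = 82.5%. These are bounds, not predictions, and they assume that every attender returns the form.

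**The case against.** The strongest reply is that the group one would most worry about, people who give up the diet, is largely covered. They are encouraged to stay in follow-up, and if they do, the week-24 assessments and the form still apply to them. That stands, and it means respondents are not restricted to people who completed the programme.

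A reader might infer from the single time point that the feasibility result as a whole describes completers only. The documents do not support this. Section 11.10 bases progression on recruitment among eligible patients, adherence among intervention participants who commenced, retention among all randomised, and safety. Satisfaction is not a criterion, so no progression decision would change.

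A reader might also infer that the reasons people leave are lost. They are not: reasons for dropout, for non-engagement and for withdrawal are recorded. What those records lack is ratings on the same items that stayers complete, so the two groups cannot be compared on them.

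A third tempting reading is that reported satisfaction could be 100% when the true figure is 69% to 81%. That needs Amber-level losses, every absentee dissatisfied and every attender satisfied. It is an extreme bound on a statistic that the protocol does not define. With the single intervention loss allowed for in section 11.3, the same extreme gives 15/16 = 94%.

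Finally, nothing in section 9.6.3 forbids posting the form to non-attenders, so a site might do so. That is fair, but staff following section 9.8 and Appendix B would have no instruction to. Asking once at week 24 is also reasonable in itself, because the form then covers all three phases. The gap is the missing route for those not present.

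**Conclusion.** The point holds in limited form. The protocol ties its only satisfaction instrument to the week-24 visit and describes no way for people who leave follow-up or miss that visit to receive it, even though the form does not need attendance. The satisfaction result can therefore be selective towards week-24 attenders.

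The likely size is 1 to 2 of 16 intervention participants (about 2 of 24 overall) at the planned dropout, and 3 to 5 of 16 at Amber retention. These counts assume that dropout means missing the week-24 visit and, for the Amber range, that losses are equal across arms. That leavers are less satisfied is plausible, but the documents do not establish it.

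This is a cheap improvement to one descriptive process measure. It does not affect the co-primary outcomes or the progression criteria.

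**What to change.** In sections 9.6.3 and 9.8 and in Appendix B, state that the same form with its pre-paid envelope is offered:

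- at the point of leaving the study, for participants who leave before week 24;
- by post at week 24, for participants who do not attend that visit;
- in neither case to anyone who has withdrawn from further communication or from data collection.

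Report the number of forms returned out of all randomised participants in each arm, so that a reader can see how complete the feedback is. This line can sit in the statistical analysis plan if preferred.

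The cost is postage for a few forms and one schedule entry with a footnote. The downside is that response from leavers will be incomplete, and with so few of them the ratings can only be described.
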